## Abstract

**Background:**

Despite advances in surgical and postoperative care, myocardial injury or infarction (MI) is still a common complication in patients undergoing coronary artery bypass surgery (CABG). Several studies that aimed to reduce postoperative myocardial injury, including those investigating statin loading, have been conducted but did not indicate any clear benefits. Evolocumab, a PCSK9 inhibitor, has been reported to lower lipids and prevent ischemic events in various medical conditions. However, the effect of evolocumab in cardiovascular surgery has not been evaluated. The objective of this trial is to evaluate the cardioprotective effects of evolocumab in elective CABG patients with multivessel coronary artery disease.

**Methods:**

EVOCABG is a prospective, randomized, open, controlled, multicenter, superiority, phase III clinical trial. Patients with multivessel coronary artery disease without initial cardiac enzyme elevation will be recruited (*n*=100). Participants will be randomly allocated into two groups: a test group (evolocumab (140mg) administration once within 72 h before CABG) and a control group (no administration). The primary outcome is the change in peak levels of serum cardiac marker (troponin-I) within 3 days of CABG surgery compared to the baseline. Secondary outcomes include post-operative clinical events including death, myocardial infarction, heart failure, stroke, and atrial fibrillation.

**Discussion:**

This trial is the first prospective randomized controlled trial to demonstrate the efficacy of evolocumab in reducing ischemic-reperfusion injury in patients undergoing CABG. This trial will provide the first high-quality evidence for preoperative use of evolocumab in mitigating or preventing ischemic-reperfusion-related myocardial injury during the surgery.

**Trial registration:**

Clinical Research Information Service (CRIS) of the Republic of Korea KCT0005577. Registered on 4 November 2020.

## Administrative information

Note: the numbers in curly brackets in this protocol refer to SPIRIT checklist item numbers. The order of the items has been modified to group similar items (see http://www.equator-network.org/reporting-guidelines/spirit-2013-statement-defining-standard-protocol-items-for-clinical-trials/).

## Introduction

### Background and rationale {6a}

Ischemic and reperfusion myocardial injury is still inevitable and is reported to be as high as 5–15% in patients that have undergone coronary artery bypass grafting (CABG) despite substantial advancements in cardiopulmonary support devices and surgical techniques [1–3].

Intraoperative myocardial injury is followed by critical complications, leading to high morbidity, mortality, and hospital expenses [4]. The mechanisms underlying ischemic and reperfusion myocardial injury during surgery are complex. In addition to direct ischemia, other factors such as thrombosis, oxygen free radicals, inflammation, endothelial dysfunction, changes in cellular metabolism, and immune reactions can lead to myocardial stunning and microvascular dysfunction [5].

A variety of clinical trials have been conducted to reduce myocardial injury during coronary artery bypass surgery. However, statins are currently the only medication approved for clinical use [6–8], although this is still an issue of debate [9, 10]. Statin, a hydroxymethylglutaryl-coenzyme A (HMG-CoA) reductase inhibitor, not only clears LDL cholesterol in the body, but is also considered cardioprotective due to its anti-inflammatory, antioxidant, and immunomodulatory effects [11–13].

Recently, PCSK9 inhibitors, a novel medication, were developed, which significantly lowers LDL cholesterol by inhibiting proprotein convertase subtilisin–kexin type 9 (PCSK9), a mediator known to degrade LDL receptors [14, 15]. Multiple studies have already proved its cardioprotective effects, and it is recommended as a standardized treatment for cardiovascular disease [15–19].

In addition to reducing cholesterol levels, PCSK9 inhibitor’s pleiotropic effects have allowed diverse applications in a variety of clinical situations. Its anti-inflammatory effects are attributed to its distribution on arterial vascular walls, which promote inflammation and atherosclerosis [20]. Furthermore, animal studies have indicated that PCSK9 inhibitors exhibit potential immunoregulatory properties, whereas septic shock models were shown to benefit from PCSK9 inhibitor administration [21]. Furthermore, Palee et al. reported that prior to administration reduces ischemic and reperfusion damage of the myocardium, thus improving cardiac function [22].

Given its potential cardioprotective effects, it can be speculated that PCSK9 inhibitors would be beneficial for patients undergoing cardiovascular surgery. However, the efficacy of PCSK9 inhibitors in patients undergoing cardiovascular surgery has not been demonstrated. We present a protocol designed to investigate the efficacy of a PCSK9 inhibitor (evolocumab) in preventing ischemic and reperfusion myocardial injury in multivessel coronary disease patients undergoing elective CABG surgery.

### Objectives {7}

This prospective, randomized, open, phase III clinical trial will evaluate the efficacy and safety of evolocumab administration prior to CABG surgery. A total of 100 patients will be recruited for a follow-up study of 1 month. The primary objective will be to assess the efficacy of evolocumab in protecting the myocardium from postoperative ischemia and reperfusion injury. The secondary objective will be to evaluate evolocumab and its relationship with various postoperative complications such as mortality, myocardial infarction, heart failure, stroke, and atrial fibrillation. Safety endpoints will be assessed based on serious adverse events, vital signs, laboratory results, relation to concomitant drugs, and clinical manifestations (left ventricular function and length of stay).

### Additional consent provisions for the collection and use of participant data and biological specimens {26b}

There are no additional studies to be done.

### Trial design {8}

In this randomized, phase III superiority controlled clinical trial, patients will be randomly assigned in a 1:1 ratio to one of two groups: a test group (evolocumab (140 mg) administration once within 72 h before CABG) and a control group (no administration). Daily blood tests will be performed during hospitalization, including those assessing cardiac markers, while major postoperative complications will be evaluated for 1 month. Medications such as aspirin and P2Y12 inhibitors (clopidogrel, prasugrel, ticagrelor) and recommended dose (2018 ACC/AHA guidelines) of statins will be given unless contraindicated [23].

## Methods

### Study setting {9}

EVOCABG will be conducted in a multicenter, university hospital (Catholic University of Korea’s Seoul St. Mary’s Hospital and Eunpyeong St. Mary’s Hospital), in the Department of Cardiothoracic Surgery. Patients from the outpatient clinic and referrals from other departments will have to provide informed consent to participate voluntarily. All participants will be assessed for eligibility based on inclusion and exclusion criteria.

### Eligibility criteria {10}

#### Primary inclusion criteria

Patients must meet the following criteria for inclusion:Age ≥19 and <85 years oldPatients with multivessel coronary artery disease (CAD) without baseline cardiac enzyme elevation, electively scheduled for CABG2-1)Grossly visible stenosis ≥ 70% of two or more coronary arteries (≥ 50% for left main artery and proximal left anterior descending artery) on coronary angiography, which is indicated for two or more vessel graft anastomoses.2-2)Cardiac biomarkers indicative of myocardial infarction, such as CK-MB, troponin-I should be within normal range.Patients who voluntarily participate and provide written informed consent signed by themselves or by a legal representativeSince elderly patients aged 75 years or older are also included in this trial, safety is considered the top priority during the selection and conduction of this trial.

#### Primary exclusion criteria

Patients meeting one or more criteria listed below shall be excluded from this trial:Previously received open heart surgeryScheduled for additional valve surgery due to valvular diseaseScheduled for emergency CABG due to myocardial infarctionPreviously treated with evolocumab or other PCSK9 inhibitors within 12 weeks before registrationActive liver disease or decreased liver function (> threefold of the normal upper limit of AST/ALT)Severe kidney dysfunction (eGFR <20 mL/min/1.73 m^2^)Major organ transplant recipients (e.g., lungs, liver, heart, bone marrow, kidney, etc.)CK-MB ≥ fivefold of the normal upper limitActive infection or hematologic, nephrological, metabolic, gastrointestinal, and endocrine disorders (determined by the investigator)Life-expectancy ≤ 1 year due to malignancy or fatal diseaseWomen of childbearing age who refuse to use medically accepted contraception or are diagnosed as pregnant on the first day of visit (unless chemical or surgical contraception has been performed or are determined to be premenopausal)Pregnant, breastfeeding patients or those who are planning a pregnancyPatients with dementia and impaired cognition or those who lack comprehension and do not comply with instructions given during the trialPatient who suffer from alcohol or drug addictionPrevious participation in another trial within 6 months before registrationUnsuitable for participation for any other reasons, as judged by the investigator

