### Sample size {14}

The objective of this trial is to evaluate whether evolocumab effectively prevents post-CABG myocardial injury in patients with multivessel CAD. The peak Troponin-I level during the first three postoperative days compared to the initial level was evaluated as the primary outcome. Based on studies by Kaushik et al. on the efficacy of statin in preventing myocardial injury in CABG patients, the difference between peak Troponin-I versus initial level was 1.00±1.34 ng/mL in the statin loaded group and 2.25±2.59 ng/mL in the control group [6]. Therefore, with the power of 0.8 and significance level of 0.05, the change of Troponin-I at the time of peak compared to the base point can be calculated as 1.00±1.34ng/mL in the evolocumab group and 2.25±2.59ng/mL in the control group. According to the Power Analysis & Sample Size (PASS) 16 program, a minimum of 45 people per group are required for validation and a potential dropout rate of 10%, 50 people per group, and a total of 100 people are required for this clinical trial.

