## Statistical methods

### Statistical methods for primary and secondary outcomes {20a}

Statistical methods for this clinical trial will be two-tailed tests with a significance level of 0.05. Continuous variables will be presented as descriptive statistics (average, standard deviation, median, minimum, and maximum). Categorical variables will be presented as descriptive statistics (frequency and percentage).

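### The contraception exclusion exempts premenopausal women, essentially the group it is written to exclude; separate pregnancy safeguards keep the resulting gap narrow

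*Protocol article*

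**What the plan says.** All of the following is in the protocol article.

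**Contraception and pregnancy (Primary exclusion criteria).** The list opens with "Patients meeting one or more criteria listed below shall be excluded from this trial". One item names women of childbearing age who decline medically accepted contraception, or who are found to be pregnant at the first visit. A parenthesis then qualifies it: "unless chemical or surgical contraception has been performed or are determined to be premenopausal". The next item excludes anyone who is pregnant, is breastfeeding or plans a pregnancy, and has no exemption. The last item lets the investigator exclude anyone judged unsuitable. The participant timeline (Table 1) schedules urine HCG at V1.

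**CK-MB (Primary inclusion and exclusion criteria).** The inclusion list opens with "Patients must meet the following criteria for inclusion". Its item 2-2 reads: "Cardiac biomarkers indicative of myocardial infarction, such as CK-MB, troponin-I should be within normal range". The exclusion list has a separate item for CK-MB at five or more times the upper limit of normal. The abstract describes the intended population in the same terms as item 2-2: "Patients with multivessel coronary artery disease without initial cardiac enzyme elevation will be recruited".

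**The concern.** An exemption should remove people for whom the exclusion is unnecessary. The first part of this one does so: it covers women who already have chemical or surgical contraception. The second part does the opposite. It releases premenopausal women from a rule about women of childbearing age, so a site following the text would have no basis in that item for excluding the women it was written for.

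What is at stake is participant protection, not inference. The criterion controls whether a woman who could become pregnant and declines contraception may be given the study drug. Such women can be screened, because the age range starts at 19 and the schedule provides for a pregnancy test.

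A smaller untidiness sits nearby. Two CK-MB limits appear in the eligibility lists, one at the upper limit of normal and one at five times that limit, with nothing to say how they relate.

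**Working it through.** No figure in the plan depends on these criteria. The sample size (45 per group, 45/0.90 = 50 after dropout, 2 × 50 = 100 in total) uses only troponin-I means and standard deviations, so the check is a reading of the rules side by side.

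**Contraception item, case by case.** Take a woman of childbearing age and apply the contraception item (A) and the separate pregnancy item (B) as written.

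- Has chemical or surgical contraception, not pregnant, not breastfeeding, plans no pregnancy: exempt under A, not caught by B. Not excluded. This is coherent.
- Premenopausal, pregnant at the first visit: named by A. If the parenthesis qualifies both halves of A, as its position allows, she is exempt from A. B excludes her regardless. Excluded, although two adjacent items then point in different directions.
- Premenopausal, declines contraception, breastfeeding or planning a pregnancy: exempt under A, excluded by B. Excluded.
- Premenopausal, declines contraception, not pregnant, not breastfeeding, plans no pregnancy: named by A, then exempt under A, and not caught by B. **Not excluded.** This is the gap.
- Not premenopausal, no chemical or surgical contraception, declines contraception: named by A and not exempt. Excluded. Read literally, the refusal rule bites only here, on the women of that age group for whom it matters least.

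The last two cases together show the inversion: the refusal rule spares the women it targets and catches the others.

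**Size of the gap.** The article gives no distribution of sex or age for the screened or enrolled patients, so no rate can be calculated. Under Trial status, 23 patients had been included, leaving 100 − 23 = 77 still to enrol. The number of enrolled women needing a check at that date was therefore at most 23, and the number in the gap may well have been zero.

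**CK-MB, by value.** Let U be the upper limit of normal.

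- CK-MB ≤ U: meets item 2-2, no exclusion applies. Eligible if all else is met.
- U < CK-MB < 5U: fails item 2-2. Ineligible, although the fivefold exclusion is silent.
- CK-MB ≥ 5U: fails item 2-2 and meets the exclusion. Ineligible twice over.

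No value is both eligible and ineligible. Because the inclusion list must be satisfied and any one exclusion suffices, the normal-range rule decides every case and the fivefold line changes none of them. It is redundant, not contradictory.

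**The case against.** The strongest reply on contraception is that this looks like a single wrong word in a journal article. The full protocol that sites work from is not shown and may read correctly. Pregnancy is excluded separately and tested for at V1, the investigator can exclude anyone unsuitable, and few candidates for multivessel CABG may be in the affected group.

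Much of that stands. A wording slip is the likeliest explanation, and whether the operational protocol shares it cannot be told from the article. The separate pregnancy item and the HCG test do close most of the apparent hole. They do not close all of it: one test at V1 and a statement that no pregnancy is planned do not replace a contraception requirement, and investigator discretion is not a rule. That the group is probably small is plausible, but the document does not quantify it.

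A reader might also infer that the two CK-MB limits contradict each other, so that sites may enrol patients with values between one and five times the upper limit. The document does not support this. An exclusion that does not apply admits nobody; the patient must still satisfy item 2-2. It is true that item 2-2 says markers "such as CK-MB, troponin-I should be within normal range", and its verb is softer than it need be, but it stands under a heading sentence that makes the inclusion list mandatory. The abstract and the consent section describe the same population without enzyme elevation.

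A reader might go further and infer a shifted baseline for the primary outcome. That does not follow either. Item 2-2 also requires a normal troponin-I, and no exclusion offers a competing troponin-I limit. A raised CK-MB baseline could enter the secondary CK-MB change variables only if a site disregarded item 2-2.

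**Conclusion.** The contraception exclusion contradicts itself as written and should be corrected. The defect is limited to non-pregnant premenopausal women who decline contraception, are not breastfeeding and plan no pregnancy. This rests on taking premenopausal in its ordinary sense, so that it essentially coincides with childbearing age, and on sites applying the published text literally.

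It would be too strong to say that the wording removes the trial's protection against exposure in pregnancy: the separate pregnancy criterion and the V1 test remain in force.

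The CK-MB lines are a minor matter of drafting. One is redundant, and no effect on the troponin-I primary outcome is shown. Nothing here changes the sample size, the power or any planned analysis.

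**What to change.** 1. Reconcile the exemption in the contraception item with the group that the item targets, and make its scope clear, so that it does not conflict with the adjacent pregnancy criterion. The sponsor and investigators should settle the clinical content; the requirement here is only that the passages agree.
2. Compare the article with the operational protocol. If the same wording is there, correct it by amendment; if not, correct the article.
3. Check women already enrolled against the reconciled rule, using information already scheduled for enrolment where it suffices.
4. As a tidy-up in the same amendment, reconcile the two CK-MB lines so that one limit is stated once, in keeping with the stated population. This review takes no position on which limit that should be.

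The cost is a line or two of text, the usual approvals for an amendment, and a record check covering at most the 23 patients included when the article was written, plus any enrolled since. No data collection or analysis needs to change.

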### Who will take informed consent? {26a}

Patients with multivessel CAD without initial elevation of cardiac markers scheduled for CABG will be assessed for eligibility according to the inclusion and exclusion criteria. Eligible participants will receive a thorough explanation of the purpose of the study and all relevant information will be provided by investigators prior to enrollment. After providing written informed consent, the demographic and smoking history of patients will be recorded in addition to the date of initialization, with other basic physical information.

### Intervention description {11a}

Evolocumab, a or PCSK9-inhibitor, is a monoclonal antibody that inhibits proprotein convertase subtilisin-kexin type 9 (PCSK9). PCSK9 is a protease expressed mostly in hepatocytes, which binds to LDL receptors, which are involved in clearing lipids and reducing serum lipid concentration. PCSK9 inhibitors inhibit LDL receptor degradation, thereby increasing lipid clearance. It is widely known that hyperlipidemia is a major risk factor for CAD, and evolocumab has emerged as a novel drug that can reduce LDL cholesterol by approximately 60%.

### Explanation for choice of comparators {6b}

To evaluate the efficacy of evolocumab, the test group will be subcutaneously administered 140 mg of the drug within 72 h prior to the operation, and the control group will receive no treatment. However, all postoperative patients will receive the same standard care as well as post-CABG medications such as aspirin 75–100 mg, P2Y12 inhibitor (e.g., clopidogrel, prasugrel, ticagrelor), unless a high bleeding tendency is noted. In addition, moderate to high doses of statins will be given, as recommended by the 2018 ACC/AHA guidelines, unless contraindicated [23].

### Criteria for discontinuing or modifying allocated interventions {11b}

Discontinuation of evolocumab may be considered in the following situations:Patient wishes to stop the administration of evolocumabInvestigator decides to discontinue the trial due to serious adverse eventsAny violation of selection or exclusion criteria or the trial protocolOccurrence of a serious disease during the clinical trialPatient receives a drug(s) without the investigator’s consent, which may possibly obscure the efficacy and safety of evolocumabPatient fails to appear for follow-up checks

### Strategies to improve adherence to interventions {11c}

Patients will be fully informed about the trial safety and methods before the administration of evolocumab. Adherence will be high due to the simple one-time administration of the drug prior to surgery. No other interventions will be given.

### Relevant concomitant care permitted or prohibited during the trial {11d}

There are no specific restrictions of concomitant care during the trial.

### Provisions for post-trial care {30}

The investigator may compensate for any harm or injury possibly caused by evolocumab administration during the trial. Patients who meet the criteria of compensation regulations are covered by insurance, in accordance with the regulations of safety and pharmaceuticals.

### Outcomes {12}

The primary outcome is the peak change in serum cardiac marker (troponin-I) within 3 days of CABG surgery compared to the baseline. The secondary outcomes include postoperative clinical events including death, myocardial infarction, heart failure, stroke, and atrial fibrillation.

### Participant timeline {13}

Table 1 shows the participant timeline.

**Table 1 Tab1:** Participant timeline

	Study period									
Visit description	Enrollment	Allocation	Intervention	Postoperation					Discharge	Close-out
Visit number	V1			V2	V3	V4	V5	V6	V7	V8
Timepoint	− 72h~0			0h±2h	6h±2h	24h±6h	48h±6h	72h±6h	7 days ± 3 days	30 days ± 5 days
**Enrollment:**										
Eligibility screen	X									
Informed consent	X									
Allocation		X								
**Intervention:**										
Evolocumab administration			X							
No medication			X							
**Assessment:**										
Demographics	X									
Medical history	X									
Vital signs, physical data^a^	X			X	X	X	X	X	X	X
Urine HCG	X									
ECG^b^	X			X		X	X	X		
Laboratory tests	X			X	X	X	X	X	X	
Concomitant drug	X			X	X	X	X	X	X	X
Outcome variables^c^	X			X	X	X	X	X	X	
Transthoracic echocardiography	X							X		
Clinical results^d^, safety evaluation			X	X	X	X	X	X	X	X

*HCG* human chorionic gonadotropin, *ECG* electrocardiogram

^a^Physical data include height and body weight

^b^ECG can be additionally performed at the discretion of the physicians

^c^Outcomes variables include primary outcomes such as cardiac enzymes

^d^Clinical results include data on death, recurrent myocardial infarction, heart failure, stroke, new-onset atrial fibrillation, and prolonged hospitalization

